**Fig. 1 Fig1:**
[figure not shown]
Flow chart of the trial design and outcome assessments. In the recruitment phase, participants fill out a questionnaire to assess their eligibility to participate. This questionnaire includes the Duke Structured Interview for Sleep Disorder Diagnosis (30 min). During weeks 0, 5 and 10, participants fill out questionnaires and sleep diaries and will wear an actigraph for subjective and objective sleep estimates, respectively. The diary is continued in all other weeks to support cognitive behavioral therapy (CBT). During weeks 1, 4, 6 and 9, participants will wear actigraphs for objective measures of compliance to chronobiological treatment

### Participants

#### Inclusion and exclusion criteria

Participants will be included that meet the criteria of an insomnia disorder as defined in the DSM-V. Furthermore, participants have to be between 18 and 70 years old. Because a meta-analysis [57] indicated that insomnia is more prevalent in females (odds ratio (OR) = 1.41), we aim for inclusion of 60 % females and 40 % males.

This study follows the Helsinki Declaration’s principles, meaning that all patients sign a written informed consent stating that participation is voluntary and that participation can be withdrawn at any time, without any negative consequences concerning their current or future treatment. Approval was obtained on 21 May 2013 from the medical ethical committee of the VU University medical center in The Netherlands (Protocol 12/472). The trial is registered at the Netherlands National Trial Register (NTR4010) [58].

Participants are recruited through the Netherlands Sleep Registry and (social) media. Interested candidates fill out a screening questionnaire regarding health status and insomnia diagnostic criteria (relevant items of Duke Structured Interview for Sleep Disorders, DSISD) [59], level of physical activity [60], light exposure (by asking about habitual hours spent outside during daylight hours) and bathing habits (frequency and duration of bathing/showering). Participants will be excluded for the following reasons:their estimated baseline level and timing of activity, bright light or body warming are already similar to the CT interventions planned;they report an eye disease incompatible with light treatment (aphakia or retinopathy), or cardiovascular or movement disorder incompatible with the exercise treatment;they report that they are currently diagnosed with a psychiatric or neurological disorder;they are shift workers, since the treatment protocol does not allow for alternative schedules, and their sleeping problems may not be due solely to insomnia; orthey use sleep medication regularly, unless they are willing and able to restrict their usage to a maximum use of twice a week, at least 1 month prior to enrollment.

### Randomization

Participants who meet the criteria and sign informed consent will be randomly assigned to CBT-I or to the waitlist and to one of the four CT conditions (including one placebo). Simple randomization will be applied to the first batch of 48 participants. During the staggered entry of subsequent participants, covariate-adaptive randomization [61] will be applied in order to maintain balanced groups throughout the study. The covariates are age, sex, use of non-sleep related medication and time of year. Since some covariates are continuous rather than categorical, randomization will be done following the method proposed by Frane [62]. This method temporarily assigns each new participant one by one to each treatment group and obtains a *P* value of the test for between-group differences for each of the covariates for that assignment, using analysis of variance (ANOVA) for continuous variables and a X^2^ test for categorical variables. This renders a *P* value for each of the four covariates for each of the eight possible assignments. The lowest of the four *P* values thus represents the least balanced covariate in that assignment situation. These lowest, or minimum, *P* values per assignment will then be used to make the actual assignment to one of the treatment conditions, where a participant will be assigned to the group for which this minimum *P* value is highest, thus resulting in a group assignment that keeps imbalance over groups as small as possible. If group sizes become unbalanced (that is, differing by more than five participants), the Frane method will be applied only to the six smallest groups instead of all eight. All randomization will be done using R [63]. Randomization will be scripted, so actual group assignment is automated.

### Study settings

All measurements and therapies are conducted at the participants’ homes, using the Internet [64, 65]. Treatment devices are sent to their homes. Participants are informed on the types of treatment used in the study and the objective of comparing them.

### Interventions

#### Cognitive behavioral therapy for insomnia

All participants will receive internet-based, personalized cognitive behavioral treatment for insomnia provided through the Somnio website for 4 weeks. The Somnio Internet therapy uses knowledge-based technology to prepare a consult and support the therapist to apply the protocol in a consistent and comprehensive way [66]. The personally assigned CBT-I therapist can adjust each consult if needed. CBT-I will consist of four consults, one every Monday morning. Every morning and evening, participants fill out the Dutch online version of the Consensus Sleep Diary [67]. The first consult will be based on the sleep diary data from the previous week, in combination with the person’s beliefs and attitude towards sleep, as assessed during week 0 by the Dysfunctional Beliefs and Attitudes towards Sleep (DBAS) questionnaire [68]. Sleep diary data of the consecutive weeks will be used to determine which cognitive and behavioral components are emphasized during the treatment [66]. A more detailed description of CBT-I has been provided earlier in this article.

#### Chronobiological treatment

##### Physical Activity

At enrolment, participants are asked to fill out questionnaires to assess their health status as well as the habitual level and timing of activity [60]. The answers on an extended Baecke questionnaire will provide the necessary information to determine the specific personalized implementation if they are randomized to the physical activity condition. More specifically, in the active treatment limb, the most intense physical activity (PA) that participants report to habitually maintain for at least half an hour (for example, (walking, running, cycling) will be (re)scheduled to be performed daily for half an hour preferably starting three hours before ideal bedtime, and never ending closer than two hours prior to ideal bedtime. The physical activity will thus at no point exceed the participants usual duration and intensity, but will be daily and set to a specific time of the day.

##### Body Warming

For body warming (BW), participants randomized to the temperature condition are instructed to take a warm bath daily for half an hour, starting 3 hours before the ideal bedtime and never ending closer than 2 hours prior to ideal bedtime. The physical activity and temperature manipulation procedures will result in elevated skin temperature at bedtime, which can enhance sleep onset [18]. If the manipulations would be done closer to bedtime, core body temperature would not have returned to baseline at bedtime and possibly interfere with sleep [18, 19].

##### Bright Light

Participants randomized to the bright light (BL) condition will receive a Philips goLITE BLU light device (HF3220/01, Philips Consumer Lifestyle, Drachten, The Netherlands). They will be instructed to install the light on a table facing a window to minimize glare by reducing contrast between relatively small bright light source and the background. The light will be set on the side, within the range of vision, but not straight across the participant. This will reduce strain on the eyes. They will be asked to sit facing the light in close proximity for half an hour at a fixed time each morning within an hour after habitual wake-up time, for example during breakfast.

##### Deactivated Ionizer

Many randomized controlled trials testing the effect of morning bright light on seasonal affective disorders (SAD), compare bright light with negative air ionization [69–72]. These studies show that morning High Density Negative Ionization (HDNI) is as effective as morning bright light treatment. Negative air ionization has been shown to positively affect cognitive performance and depression [73]. The application has not been evaluated for its possible effect on insomnia. In one study on SAD, a deactivated ionizer (DI) was used as placebo condition [74]. The ionizer was modified to suggest normal functioning, as indicated by airflow, while negative ion production had been deactivated. Treatment outcome expectancy for the (deactivated) negative ionizer was equal to that of BL. In the present study, participants randomized to the placebo treatment will therefore receive a likewise deactivated ionizer (DI) device (Ionic Air Purifier, XJ-2100, Shanghai Neo.Tec Electron Co., Ltd, Shanghai, China). Participants will be instructed to install the device on a table where they can sit in close proximity to it for half an hour each morning at their earliest convenience after ideal wake-up time, for example during breakfast. This placebo has been applied successfully in several studies in the USA [69, 74], but not yet in the Netherlands, making it unlikely to be recognized as a placebo.

### Assessments and outcomes

To assess subjective sleep parameters as well as daytime complaints, participants will be keeping a diary in the morning and evening for the entire 11-week protocol. Sleep is assessed in the morning using the Dutch version of the Consensus Sleep Diary [67]. Primary outcome, sleep efficiency (the percentage of time slept during the time in bed for sleep), is calculated from the sleep diary variables as follows:$$ SE\kern0.5em =\kern0.5em \frac{\left( LightOn\kern0.5em -\kern0.5em  LightOff\right)\kern0.5em -\kern0.5em  SOL\kern0.5em -\kern0.5em  WASO\kern0.5em -\kern0.5em EMA}{LightOn-\kern0.5em  LightOff} $$

where *SE* is sleep efficiency; *LightsOn* is the moment people indicated they stop trying to sleep, calculated from their final wake up time and time they stayed in bed to try to fall asleep again; *LightsOff* is the time people turn off the lights and/or disengage from activities to go to sleep; *SOL* is sleep onset latency; *WASO* is the time awake after sleep onset; and *EMA* is early morning awakening, or the time people spend trying to fall back asleep after final awakening.

Daytime functioning is assessed in the evening using a dedicated questionnaire on all complaints listed in the DSM-V and the International Classification of Sleep Disorders, 2nd edition (ICSD-2). During week 0, participants will fill out the complete Duke Structured Interview for Sleep Disorders in order to have a complete overview of sleep complaints and other medical and psychological complaints they currently have or have had in the past.

During weeks 0, 5 and 10, participants will fill out a comprehensive set of questionnaires:Expectations or subjective outcome of the selected treatments;Health-related costs during the last 4 weeks (Trimbos/iMTA questionnaire for Costs associated with Psychiatric Illness: TiC-P) [75];Functional health (Quality of Life Questionnaire, Short Form 36, SF-36) [76];Depression and anxiety (Hospital Anxiety and Depression Scale, HADS) [77];Mood (Positive Affect, Negative Affect Scale, PANAS) [78];Experience of pleasure and comfort (Temporal Experience of Pleasure Scale, TEPS) [79];Thoughts during resting state (Amsterdam Resting State Questionnaire, ARSQ) [55]Hyperarousal. Because this is considered a key feature of insomnia, it is queried using four different scales; the Arousal Predisposition Scale (APS) [80]; the Hyper Arousal Scale (HAS) [81]; the adult ADHD Self-Report Scale (ASRS) [82]; and the Pre-Sleep Arousal Scale (PSAS) [83];Insomnia severity (Insomnia Severity Index, ISI) [84];Beliefs and attitudes regarding sleep (DBAS) [68];Sleep effort (Glasgow Sleep Effort Scale, GSES) [85];Sleep self-efficacy (Sleep Self-Efficacy Scale, SSES) [86];Sleep locus of control (SLOC) [87].

As shown in Fig. 1, ambulatory recordings will be performed during the baseline week and the first week of treatment (weeks 0 and 1), the last week of the CT treatment period and the first week following completion (weeks 4 and 5), and during weeks 9 and 10. During these weeks, participants will continuously wear a wrist actigraph to estimate sleep and light exposure (Philips Actiwatch Spectrum, Philips Respironics, Murrysville, PA, USA) and an accelerometer worn on the trunk to estimate energy expenditure (Philips DirectLife, DL8700/01, Philips, Eindhoven, The Netherlands).

### Compliance

#### CBT-I

Compliance with some aspects of CBT-I, for example sleep restriction and stimulus control, can be monitored using the sleep diary combined with the actigraphic sleep estimates.

#### CT

Compliance with the chronobiological treatments will be monitored by means of questions added to the sleep diaries. Moreover, objective measures of compliance for BL and PA can be derived from ambulatory monitoring of physical activity and light exposure by the Actiwatch Spectrum and DirectLife devices. Participants randomized to BL are instructed to expose the Actiwatch Spectrum to the light when sitting in front of the goLite BLU. Participants assigned to BW receive a digital bath thermometer (type: Lotus, Béaba, Oyonnax Cedex, France) and are asked to register temperature of the bathing water to monitor compliance with the body warming treatment.

### Outcome measures

The primary outcome measure is the change from week 0 to week 5 in subjective sleep efficiency derived from the sleep diary. Secondary subjective sleep estimates include difficulties falling asleep, difficulties maintaining sleep, early morning awakening and non-restorative sleep. A secondary outcome regarding daytime consequences is the average rating of evening diary ratings on eighteen major daytime functioning complaints. Ancillary analyses on persistence of treatment use the same variables obtained in week 10.

Actigraphically estimated objective sleep parameters (sleep efficiency, sleep onset latency, sleep duration, wake after sleep onset, and the average durations of uninterrupted periods of sleep and wakefulness) are secondary outcome measures meant to complement the subjective evaluations. These are calculated from the ActiWatch Spectrum recordings using the Respironics Actiware software (version 5.71.0, Philips Respironics, Murrysville, PA, USA). Given the variability in subjective [88] and objective [89] sleep estimates, they will be assessed for 7 subsequent days at each assessment. Additional questionnaires, assessed in weeks 0, 5 and 10, will provide secondary outcome measures (see the list above). Specifically, the direct and indirect medical costs (TiC-P) will be included.

### Effect moderation by subtype score

Preliminary results of the Latent Class Analysis on comprehensive psychometric data of a large sample of participants of the Netherlands Sleep Registry suggests the existence of four different subtypes of insomnia, each with about equal prevalence. From the extensive number of questionnaires on traits these volunteers filled out, we are presently selecting the minimal subset of questions required to obtain good estimates of the a posteriori probabilities of a participant to belong to each one of the four classes. These items will be included in a Sleep Subtype Survey that will be assessed in all participants of the present RCT. The resulting four Insomnia Subtype Probabilities (ISP) will be included in analyses aimed at evaluating treatment effect moderation by each of the four insomnia subtype probabilities.

### Statistical analysis

#### Data reduction and reporting

The data of qualitative variables (for example, gender, type of treatment, and insomnia subtype) will be presented as incidence rates (number and percent). The data of continuous variables (for example, age, measures derived from sleep diaries, questionnaires and actigraphy) will be presented by measures of central tendency (that is, mean and median) and dispersion (that is, standard deviation and range).

#### Treatment effects and moderation estimates

Mixed effect models will be applied to estimate all time by treatment effects, time by treatment interaction effects and effect moderation by the individual’s insomnia subtype probabilities. For each outcome measure, all effects will be estimated simultaneously in one single linear regression equation. The primary outcome measure of sleep efficiency will be illustrated below. The diary and actigraphy based outcome measures have a two-level hierarchical data-structure: repeated measures of 14 diary inputs *i* across T0 and T1 are nested within subjects *j*. The 14*160 = 2,240 data points can be used to estimate simultaneously all effects ß using the following mixed effect model:$$ \begin{array}{l}\mathrm{S}{\mathrm{E}}_{\mathrm{ij}}\kern0.5em =\kern0.5em {\mathrm{\ss}}_{0\mathrm{i}\mathrm{j}}\kern0.5em +\kern0.5em {\mathrm{\ss}}_1*{\mathrm{Time}}_{\mathrm{ij}}\kern0.5em +\kern0.5em {\mathrm{\ss}}_2*\mathrm{C}\mathrm{B}\mathrm{T}\hbox{-} {\mathrm{I}}_{\mathrm{j}}\kern0.5em +\kern0.5em {\mathrm{\ss}}_3*\mathrm{B}{\mathrm{L}}_{\mathrm{j}}\kern0.5em +\kern0.5em {\mathrm{\ss}}_4*\mathrm{P}{\mathrm{A}}_{\mathrm{j}}\kern0.5em +\kern0.5em {\mathrm{\ss}}_5*\mathrm{B}{\mathrm{W}}_{\mathrm{j}}\kern0.5em +\kern0.5em {\mathrm{\ss}}_6*\mathrm{IS}{\mathrm{P}}_{\mathrm{j}}\kern0.5em +\kern0.5em {\mathrm{\ss}}_7*\mathrm{T}\mathrm{i}\mathrm{m}{\mathrm{e}}_{\mathrm{ij}}*\mathrm{IS}{\mathrm{P}}_{\mathrm{j}}+\\ {}\kern0.5em {\mathbf{\ss}}_{\mathbf{8}}*\mathbf{C}\mathbf{B}\mathbf{T}\hbox{-} {\mathbf{I}}_{\mathbf{j}}*\mathbf{T}\mathbf{i}\mathbf{m}{\mathbf{e}}_{\mathbf{ij}}\kern0.5em +\kern0.5em {\mathrm{\ss}}_9*\mathrm{C}\mathrm{B}\mathrm{T}\hbox{-} \mathrm{I}*\mathrm{IS}{\mathrm{P}}_{\mathrm{j}}\kern0.5em +\kern0.5em {\mathbf{\ss}}_{\mathbf{10}}*\mathbf{C}\mathbf{B}\mathbf{T}\mathbf{\hbox{-} }{\mathbf{I}}_{\mathbf{j}}*\mathbf{T}\mathbf{i}\mathbf{m}{\mathbf{e}}_{\mathbf{ij}}*\mathbf{I}\mathbf{S}\mathbf{P}+\\ {}\kern0.5em {\mathbf{\ss}}_{\mathbf{11}}*\mathbf{B}{\mathbf{L}}_{\mathbf{j}}*\mathbf{T}\mathbf{i}\mathbf{m}{\mathbf{e}}_{\mathbf{ij}}\kern0.5em +\kern0.5em {\mathrm{\ss}}_{12}*\mathrm{B}\mathrm{L}*\mathrm{IS}{\mathrm{P}}_{\mathrm{j}}\kern0.5em +\kern0.5em {\mathbf{\ss}}_{\mathbf{13}}*\mathbf{B}{\mathbf{L}}_{\mathbf{j}}*\mathbf{T}\mathbf{i}\mathbf{m}{\mathbf{e}}_{\mathbf{ij}}*\mathbf{I}\mathbf{S}{\mathbf{P}}_{\mathbf{j}}+\\ {}\kern0.5em {\mathbf{\ss}}_{\mathbf{14}}*\mathbf{P}{\mathbf{A}}_{\mathbf{j}}*\mathbf{T}\mathbf{i}\mathbf{m}{\mathbf{e}}_{\mathbf{ij}}\kern0.5em +\kern0.5em {\mathrm{\ss}}_{15}*\mathrm{P}\mathrm{A}*\mathrm{IS}{\mathrm{P}}_{\mathrm{j}}\kern0.5em +\kern0.5em {\mathbf{\ss}}_{\mathbf{16}}*\mathbf{P}{\mathbf{A}}_{\mathbf{j}}*\mathbf{T}\mathbf{i}\mathbf{m}{\mathbf{e}}_{\mathbf{ij}}*\mathbf{I}\mathbf{S}{\mathbf{P}}_{\mathbf{j}}+\\ {}\kern0.5em {\mathbf{\ss}}_{\mathbf{17}}*\mathbf{B}{\mathbf{W}}_{\mathbf{j}}*\mathbf{T}\mathbf{i}\mathbf{m}{\mathbf{e}}_{\mathbf{ij}}\kern0.5em +\kern0.5em {\mathrm{\ss}}_{18}*\mathrm{B}\mathrm{W}*\mathrm{IS}{\mathrm{P}}_{\mathrm{j}}\kern0.5em +\kern0.5em {\mathbf{\ss}}_{\mathbf{19}}*\mathbf{B}{\mathbf{W}}_{\mathbf{j}}*\mathbf{T}\mathbf{i}\mathbf{m}{\mathbf{e}}_{\mathbf{ij}}*\mathbf{I}\mathbf{S}{\mathbf{P}}_{\mathbf{j}}+\\ {}\kern0.5em {\mathrm{\ss}}_{20}*\mathrm{C}\mathrm{B}\mathrm{T}\hbox{-} {\mathrm{I}}_{\mathrm{j}}*\mathrm{B}{\mathrm{L}}_{\mathrm{j}}\kern0.5em +\kern0.5em {\mathbf{\ss}}_{\mathbf{21}}*\mathbf{C}\mathbf{B}\mathbf{T}\mathbf{\hbox{-} }{\mathbf{I}}_{\mathbf{j}}*\mathbf{B}{\mathbf{L}}_{\mathbf{j}}*\mathbf{T}\mathbf{i}\mathbf{m}{\mathbf{e}}_{\mathbf{ij}}\kern0.5em +\kern0.5em {\mathrm{\ss}}_{22}*\mathrm{C}\mathrm{B}\mathrm{T}\hbox{-} {\mathrm{I}}_{\mathrm{j}}*\mathrm{B}{\mathrm{L}}_{\mathrm{j}}*\mathrm{IS}{\mathrm{P}}_{\mathrm{j}}\kern0.5em +\kern0.5em {\mathbf{\ss}}_{\mathbf{23}}*\mathbf{C}\mathbf{B}\mathbf{T}\hbox{-} \\ {}\kern0.5em {\mathbf{I}}_{\mathbf{j}}*\mathbf{B}{\mathbf{L}}_{\mathbf{j}}*\mathbf{T}\mathbf{i}\mathbf{m}{\mathbf{e}}_{\mathbf{ij}}*\mathbf{I}\mathbf{S}\mathbf{P}+\\ {}\kern0.5em {\mathrm{\ss}}_{24}*\mathrm{C}\mathrm{B}\mathrm{T}\hbox{-} {\mathrm{I}}_{\mathrm{j}}*\mathrm{P}{\mathrm{A}}_{\mathrm{j}}\kern0.5em +\kern0.5em {\mathbf{\ss}}_{\mathbf{25}}*\mathbf{C}\mathbf{B}\mathbf{T}\mathbf{\hbox{-} }{\mathbf{I}}_{\mathbf{j}}*\mathbf{P}{\mathbf{A}}_{\mathbf{j}}*\mathbf{T}\mathbf{i}\mathbf{m}{\mathbf{e}}_{\mathbf{ij}}\kern0.5em +\kern0.5em {\mathrm{\ss}}_{26}*\mathrm{C}\mathrm{B}\mathrm{T}\hbox{-} {\mathrm{I}}_{\mathrm{j}}*\mathrm{P}{\mathrm{A}}_{\mathrm{j}}*\mathrm{IS}{\mathrm{P}}_{\mathrm{j}}\kern0.5em +\kern0.5em {\mathbf{\ss}}_{\mathbf{27}}*\mathbf{C}\mathbf{B}\mathbf{T}\mathbf{\hbox{-}}\\ {}\kern0.5em {\mathbf{I}}_{\mathbf{j}}*\mathbf{P}{\mathbf{A}}_{\mathbf{j}}*\mathbf{T}\mathbf{i}\mathbf{m}{\mathbf{e}}_{\mathbf{ij}}*\mathbf{I}\mathbf{S}\mathbf{P}\mathbf{j}+\\ {}\kern0.5em {\mathrm{\ss}}_{28}*\mathrm{C}\mathrm{B}\mathrm{T}\hbox{-} {\mathrm{I}}_{\mathrm{j}}*\mathrm{B}{\mathrm{W}}_{\mathrm{j}}\kern0.5em +\kern0.5em {\mathbf{\ss}}_{\mathbf{29}}*\mathbf{C}\mathbf{B}\mathbf{T}\mathbf{\hbox{-} }{\mathbf{I}}_{\mathbf{j}}*\mathbf{B}{\mathbf{W}}_{\mathbf{j}}*\mathbf{T}\mathbf{i}\mathbf{m}{\mathbf{e}}_{\mathbf{ij}}\kern0.5em +{\mathrm{\ss}}_{30}*\mathrm{C}\mathrm{B}\mathrm{T}\hbox{-} {\mathrm{I}}_{\mathrm{j}}*\mathrm{B}{\mathrm{W}}_{\mathrm{j}}*\mathrm{IS}{\mathrm{P}}_{\mathrm{j}}\kern0.5em +\kern0.5em {\mathbf{\ss}}_{\mathbf{31}}*\mathbf{C}\mathbf{B}\mathbf{T}\mathbf{\hbox{-}}\\ {}\kern0.5em {\mathbf{I}}_{\mathbf{j}}*\mathbf{B}{\mathbf{W}}_{\mathbf{j}}*\mathbf{T}\mathbf{i}\mathbf{m}{\mathbf{e}}_{\mathbf{ij}}*\mathbf{I}\mathbf{S}{\mathbf{P}}_{\mathbf{j}}\end{array} $$

In this regression equation, SE = sleep efficiency; ß_0ij_ = intercept; time denotes the post intervention (T1) versus baseline (T0) assessment week; CBT = cognitive behavior therapy assignment; BL = bright light assignment; PA = physical activity assignment; BW = body warming assignment; ISP = insomnia subtype probability; and ß_1_ to ß_31_ denote effect estimates. The effects and terms of interest are shown in bold font. For example, line 2 shows in bold font the overall treatment by time interaction effect **ß**_**8**_ of CBT-I versus waitlist and the moderation of this effect **ß**_**10**_ by one’s insomnia subtype probability. Lines 3 to 5 show the corresponding effect estimates for BL, PA and BW interventions, and lines 6 to 8 the for their interaction with CBT-I. For clarity, the regression equation shows only one of the four expected ISPs. Wald tests will be used to evaluate the significance of the effect estimates. Statistical significance is thresholded at p = 0.05. The simultaneous estimation of all effects of interest in a single regression model compensates for multiple comparisons. Mixed effect model analyses will be implemented in MLwiN (version 2.02, Centre for Multilevel Modelling, University of Bristol, Bristol, UK.) and (R: A language and evironment for statistical computing, R Foundation for Statistical Computing, Vienna, Austria.).

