## Methods/Design

### Trial design

The study is a double blind, randomized, placebo controlled trial. Aiming at 160 participants who complete the trial, with a dropout rate of 10 %, 180 participants will be recruited, who will be randomly assigned to one of eight limbs in a repeated measures design with two factors (CBT-I and CT), of respectively 2 levels (active CBT-I treatment versus waitlist monitoring) and 4 levels (light, physical activity, body warming and placebo) (see Fig. 1). Covariate-adaptive randomization aims at an equal representation of insomnia subtypes within each treatment limb. Assessment will be performed at baseline (week 0), after a 4-week treatment period (week 5), and after a second 4-week treatment/monitoring period (week 10).

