### Power and sample size

#### Statistical power estimates

The statistical power of mixed effect regression models with seven repeated measures (diaries) both before and after intervention have been calculated according to the equations given by Twisk, page 280 [90], similar to those calculations made in a previous repeated measures RCT that we published [91]. Statistical power calculations on repeated measures require an estimate of the intraclass correlation coefficient (ICC, that is, within-subject). We estimated the ICC for the primary outcome measure of subjective sleep efficiency from the 9-day sleep diaries [67] that we recently assessed through the internet for 27 people suffering from insomnia according to an Insomnia Severity Index ≥10 [92]. In agreement with the robust observation that night-by-night sleep variability is an intrinsic part of the insomnia symptomatology (reviewed in [88]), we found only a moderate ICC of 0.27, supporting the use of repeated assessment of the primary outcome measure to increase statistical power of the design.

Given this moderate ICC of 0.27, seven pre-assessments at T0, and seven post-assessments at T1, the 160 completing participants provide a power 1-beta of 0.80 to allow for the detection, at a significance of alpha = 0.05, of even small to medium main effects of CBT-I (minimal detectable difference d = 0.27 standard deviations), of each of the three CTs (d = 0.31) and of their interaction with CBT-I (d = 0.41). The minimally detectable difference in the time by treatment interaction between any two types of CT is small to medium as well (d = 0.38).

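### The printed model contrasts raw change scores; adjusting for week-0 sleep efficiency would cut the variance of every effect of interest by about 14% on the plan's own inputs

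*Protocol article*

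**What the plan says.** The Outcome measures section defines the endpoint: "The primary outcome measure is the change from week 0 to week 5 in subjective sleep efficiency derived from the sleep diary". Under Trial design, participants are "randomly assigned to one of eight limbs in a repeated measures design with two factors (CBT-I and CT"), with two CBT-I levels and four CT levels. Treatment effects and moderation estimates sets the analysis: "Mixed effect models will be applied to estimate all time by treatment effects, time by treatment interaction effects".

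The model places the week-0 and week-5 diary nights in one outcome vector, nested within persons. Of its 32 coefficients (ß0 to ß31):

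- 14 are bold and contain both Time and a treatment: ß8, ß10, ß11, ß13, ß14, ß16, ß17, ß19, ß21, ß23, ß25, ß27, ß29 and ß31. The text below the equation calls these the effects of interest; for CBT-I, "line 2 shows in bold font the overall treatment by time interaction effect" of CBT-I against waitlist.
- 14 contain a treatment but not Time: ß2–ß5, ß9, ß12, ß15, ß18, ß20, ß22, ß24, ß26, ß28 and ß30.
- Four contain no treatment: ß0, ß1, ß6 and ß7.

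Nothing in the article makes the limbs share a week-0 mean or enters week-0 sleep efficiency as a covariate. It is also not among the four covariates balanced under Randomization (age, sex, non-sleep medication, time of year).

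**The concern.** The intercept with ß2–ß5, ß20, ß24 and ß28 makes eight free week-0 means for eight limbs. The other seven limb terms without Time free the week-0 subtype slope in each limb. With week 0 fitted exactly in this way, each bold effect is the week-5 contrast minus the whole of the week-0 contrast.

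If week-0 diaries are unaffected by allocation, any week-0 difference between randomized limbs is chance. Only part of that chance difference carries forward to week 5, namely a fraction equal to the regression slope of week 5 on week 0. Subtracting all of it adds noise. Baseline adjustment subtracts only the part that predicts.

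What is at stake is precision, with about 20 completers per limb. The loss falls on all 14 bold effects alike, including the CBT-I by CT interactions and their subtype moderation, for which the article reports its largest detectable differences (d = 0.41 and 0.55).

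**Working it through.** **Inputs (Statistical power estimates).** ICC 0.27; seven nights before and seven after; "the 160 completing participants", so about 20 per limb; "at a significance of alpha = 0.05"; "provide a power 1-beta of 0.80". Two-sided testing is assumed, because it reproduces the stated figures. Variances are in units of the single-night variance.

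**Step 1: the plan's own figures.** The variance of a seven-night mean is f = (1 + 6 × 0.27)/7 = 0.3743. With d = √[(1.960 + 0.842)² × f × (1/n₁ + 1/n₂)]:

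| Contrast | n₁ / n₂ | Computed d | Stated d |
|---|---|---|---|
| CBT-I | 80 / 80 | 0.271 | 0.27 |
| Each CT | 40 / 120 | 0.313 | 0.31 |
| CT by CBT-I | 20 / 140 | 0.410 | 0.41 |
| CT against CT | 40 / 40 | 0.383 | 0.38 |

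The figures reproduce as comparisons of the post-treatment week mean. They make no use of week 0, so they describe neither the planned contrast nor the adjusted one.

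**Step 2: planned against adjusted variance.** Under a random intercept with equal week variances, the two week means correlate ρ = 0.27/0.3743 = 0.721.

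- Planned (change score): 2f(1 − ρ) = 2 × 0.3743 × 0.279 = 0.2086.
- Adjusted for week 0: f(1 − ρ²) = 0.3743 × 0.480 = 0.1795.
- Ratio: (1 + ρ)/2 = 0.861, a cut of 13.9% in variance. √0.861 = 0.928, a cut of about 7% in standard error.

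An exact generalized least squares comparison of the 32-term equation with the 18-term equation (20 per limb, one centred subtype probability, complete diaries) gives 0.861 for all 14 bold coefficients. A simulation of 4,000 trials with a true CBT-I effect of 0.300 gave a mean of 0.302 for both estimators. The variance was 13–14% lower with adjustment.

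**Step 3: what that buys.** An effect with 80% power under the plan lies 2.802 standard errors from zero. After adjustment it lies 2.802/0.928 = 3.02 away, and 3.02 − 1.96 = 1.06 gives power of 85.5%. This is equivalent to 160/0.861 = 186 completers. For an 80-against-80 contrast the detectable difference moves from 0.202 to 0.188.

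**Step 4: sensitivity to the correlation.** The documents give no week-0/week-5 correlation. With equal variances the cut is (1 − ρ)/2:

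| ρ | Variance cut | Power where the plan has 80% |
|---|---|---|
| 0.80 (assumed) | 10% | 84% |
| 0.72 (from the plan's ICC) | 13.9% | 85.5% |
| 0.60 (assumed) | 20% | 88% |
| 0.50 (assumed) | 25% | 90% |

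**Step 5: sensitivity to unequal variances.** Let k be the week-5 SD divided by the week-0 SD. In units of the week-0 variance, planned = 1 + k² − 2ρk and adjusted = k²(1 − ρ²). At ρ = 0.721 and k = 1.2 these are 0.709 and 0.691, ratio 0.975, a cut of about 2.5%. The gain vanishes at k = 1/ρ = 1.39.

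**Step 6: reporting shifts.** Suppose knowledge of the limb shifts the diaries of one group by d.

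| Shift present in | Bias, planned | Bias, adjusted |
|---|---|---|
| Week 0 only | d | ρd = 0.72d |
| Both weeks | 0 | (1 − ρ)d = 0.28d |

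Simulation with d = 0.10 agreed: bias 0.10 against 0.07 in the first case, and estimates of 0.299 against 0.328 for a true 0.30 in the second.

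**The case against.** The strongest reply is that nothing here is an error. A model with all treatment and Time terms is conventional, is unbiased, and directly estimates the change that the protocol names as its outcome. This stands, and a reader should not infer that the planned analysis is biased or invalid. It does not remove the gain: adding the week-0 mean as a covariate leaves the estimated effect the same whether the outcome is the week-5 value or the change, so the primary outcome definition need not move.

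Three stronger readings are tempting, and the documents do not support them.

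- **That the gain is 14–25% whatever the covariance.** Only the 14% follows from the plan's figures. The 25%, and with it a fall in the CBT-I detectable difference from 0.271 to 0.235 and a rise in power from 80% to 90%, needs an assumed correlation of 0.5. Greater variance at week 5 shrinks the gain, and the article itself expects heterogeneous response.
- **That the change costs nothing.** Participants cannot be blinded, and Blinding and expectation assessment has them rate their assigned treatments at T0 after randomization. If allocation colours both diary weeks equally, the planned contrast cancels the shift and the adjusted one keeps 28% of it.
- **That the 14 terms can only reflect chance.** This needs week-0 diaries that precede disclosure of the limb. It also needs care over dropout, since the model is illustrated on 160 completers while "with a dropout rate of 10 %, 180 participants will be recruited". With differential dropout, completers' week-0 means could truly differ between limbs.

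On scale, at the stated CBT-I difference of 0.27 for 80 against 80, the plan's ICC already gives about 96% power, and adjustment raises it to 98%. That contrast is also not ß8 itself: with 0/1 indicators and the CBT-I by CT terms present, ß8 compares about 20 with 20 within the placebo CT. The gain matters more for such cell-level and interaction effects.

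**Conclusion.** The point holds as one of efficiency. As printed, the model discards precision that the collected week-0 diaries could supply. On the plan's own ICC the loss is about 14% of variance (7% of standard error) for each of the 14 bold effects, or 80% against about 85.5% power at an effect where the planned contrast has 80%.

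This rests on a random intercept, equal variances in the two weeks, complete diaries, and week-0 reports that are unaffected by allocation. The size is uncertain in both directions: 25% at an assumed correlation of 0.5, about 2.5% if the week-5 SD is 1.2 times the week-0 SD. Whether week-0 diaries precede disclosure cannot be settled from the article.

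**What to change.** 1. Adjust the primary analysis for week 0. The preferred form analyses the week-5 nights with each person's week-0 mean sleep efficiency as a covariate. The alternative keeps both weeks in the outcome and drops the 14 limb terms without Time, leaving ß0, ß1, ß6, ß7 and the 14 bold terms (18 coefficients), with one common week-0 mean and one common subtype slope. The seven limb-by-subtype terms without Time must go too if the moderation effects are to share the gain.
2. Show week-0 means per limb descriptively.
3. Keep the printed 32-term model as a sensitivity analysis, because it is the safer one if reporting is shifted in both weeks.
4. State whether week-0 diaries are completed before participants learn their limb. If they are not, say why the adjusted analysis is still preferred.

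The cost is wording in the analysis plan, with no new data. The article reports recruitment as ongoing and treatment codes as closed until the dataset is final, so the change can be made before unblinding.
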